**Randomisation and blinding**

Participants will be randomly allocated in a 1:1 ratio to either intervention or control group arms. Randomising of study participants will be done according to the random number generator from <https://www.random.org/integers/?num=220&min=1&max=220&col=5&base=10&format=html&rnd=new>. Participants allocated even numbers will be cases and participants allocated odd numbers will be controls. Participants randomized in the control arm will be blinded to the intervention. Due to the nature of the intervention, it will not be possible to blind the investigators. However, to minimize bias, all participants will be allocated a study ID and all data will be collated using the study ID. Analysis of the data will be conducted by blinded investigators.

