**Sample size**

Sample size calculations are focused on two different measures and were also done assuming equal numbers of participants in each group. The first measure takes into account an absolute increase in mean adherence of 15 % (Hulley et al., 2013). In this measure, at two tailed 0.05 significance level with a power of 80 % and standard deviation of 35 (Goldstein et al 2014), the number of participants required in each group is 86. In the second measure, the analysis is by comparing proportions of adherence (Hulley et al., 2013). Previous studies have estimated the adherence to cardiovascular drugs to be up to 60 % (Chowdhury et al., 2013; Bowry et al., 2010). In this measure, a total sample size of 182 participants is needed to provide 80 % power to detect an increase in the proportion of adherent participants from 60 % to 80 %, with a two tailed 0.05 significance level. Therefore, taking the larger of the two sample sizes (91 participants in each arm), and allowing for a 20 % loss to follow up, a total of 220 participants will be recruited in this study with each arm consisting of 110 participants.

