**Trial data collection**

Trial data will be collected at 4 time points (at baseline, 3, 6 and 9 months). Data will be collected at face-to-face during home visits, phone calls or via skype interviews (mainly for rural participants). To encourage participant retention and completeness of data, participants will receive a honourarium of AUD$30 in total at completion of the study.

At the point of recruitment into the trial, baseline data will be collected after written informed has been obtained by a member of the research team. The following information will be collected:

Sociodemographic information: Date of birth, gender, ethnicity, height, weight, education status, marital status, employment status, smoking status and health literacy

Medical history: comorbidities, NYHA class, standardised mini-mental state exam score, depression score, all prescribed and non-prescribed medication history

Laboratory test results: full blood counts, full electrolytes (sodium, potassium, urea, creatinine +/- magnesium), Hb, iron studies, NT pro BNP, liver function tests.

Functional assessment: QoL questionnaire using the Short Form 36 Health Survey version 2 (SF-36v2) (Ware JE; RAND Corporation 2015), Depression Anxiety and Stress Scales (DASS), Self-Care of Heart Failure Index (SCHFI) (Riegel et al., 2009), EQ-5D-5L questionnaire (Herdman et al., 2011) and drug adherence questionnaire, healthcare utilization (linkage data from Australian Pharmaceutical benefits Scheme and Medicare Benefits Schedule).

At the 3, 6 and 9 month follow ups, a member of the research team will record details of any changes to the participants’ medication or implantable cardiac devices, details of any hospitalisations or healthcare resource utilization since the last follow up. At each follow up interview, participants in the control arm will be asked whether they have used any drug administration aids or medication reminder app or other forms of electronic reminder systems for daily administration of medications. At the end of the study, intervention arm participants will complete a satisfaction survey to assess the acceptability, utility and engagement with the NPS MedicineWise application. Also, data about prescription refill rates and healthcare utilization will be gathered for all participants through data linkage with the Australian Pharmaceutical benefits Scheme and Medicare Benefits Schedule.

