**Process evaluation**

**Economic evaluation**

A rigorous and systematic approach to the economic analysis will be applied applying international standard best practice methods for the design and conduct of economic evaluations in health care (Drummond et al., 2015; Brazier et al., 2016). The cost-effectiveness of the proposed intervention will be estimated using a cost-utility analysis (CUA) undertaken alongside the RCT with quality adjusted life years gained (QALYs) as measured by the EQ-5D-5L as the main measure of outcome. The purpose of the economic evaluation is to compare the differences in the streams of outcomes and resource use that will occur as a consequence of the introduction of the mobile phone app. This will be expressed in terms of the incremental cost per QALY gained in the Australian setting. A health system perspective will be taken for the economic evaluation including health related resource use (costs and cost-offsets) and health related quality of life outcomes. As the economic evaluation will be conducted alongside the clinical trial with a 9 month follow up period, discounting of costs and benefits beyond the base year of the economic evaluation will not be necessary. The setting of the economic evaluation will be the Australian health care setting.

The intervention will be tested in the RCT in the circumstances in which it will be expected to be applied should it be adopted for wide-spread routine application within the health system. The main clinical outcomes of the RCT encapsulate directly measured and reported participant relevant end points. The follow up period of 9 months is an appropriate time horizon within which all patient relevant end points will be adequately captured.

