**Data analysis**

The primary analyses will be based on a between-group (intervention arm vs control arm), intention-to-treat approach at the different time points. Continuous variables will be analysed using independent t-tests and discreet variables will be analyses using chi-squared tests. Where appropriate, other statistical tests will be employed depending on the nature of the data. Identification of any confounding baseline variables will be corrected by logistic regression analysis. All between group outcome results that are significant will be reported with odds ratios and 95 % confidence intervals. Statistical significance is set at α 0.05.

Qualitative outcomes

Thematic analysis will be carried out based on patient responses to open-ended questions in the functional assessments. This will enable to generate emerging and overarching themes. The analysis will characterise intervention arm participants’ observed and self-reported responses to the intervention and link these responses to the acceptability, utility and their engagement with the smartphone app. This thematic analysis will be based on the intervention arm participants’ responses collected at months 3 and 9, in addition to a satisfaction survey undertaken upon completion of the trial.

Economic outcomes

Data on the frequency and duration of hospital in-patient admissions will be obtained from medical records, and PBS and MBS utilisation data from Medicare following informed patient (or proxy in the case of moderate to severe cognitive impairment) consent. Unit costs will be derived from relevant hospital finance departments, published data sets including Pharmaceutical Benefits Scheme and Medicare Benefits Schedule and Australian Refined Diagnosis Related Groups (AR-DRG) cost weights.

A participant level analysis will be undertaken to determine the incremental costs and outcomes associated with the intervention relative to controls. Incremental cost effectiveness ratios and their associated confidence intervals will be estimated and cost effectiveness acceptability curves for varying threshold values of cost effectiveness will also be presented. An assessment of the sensitivity of the results obtained to variation in measured resource use, effectiveness and/or unit costs will be undertaken using appropriate one-way, multi-way and probabilistic sensitivity analysis.

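### The only baseline adjustment the protocol names is logistic regression, which cannot be applied to QALYs or costs, and the economic analysis names no other

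*Protocol*

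**What the plan says.** The Economic evaluation section of the protocol plans a cost-utility analysis alongside the trial, with "quality adjusted life years gained (QALYs) as measured by the EQ-5D-5L as the main measure of outcome". It commits in general terms to best-practice methods for economic evaluation but names no estimator.

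Under Data analysis, the Economic outcomes text says that "A participant level analysis will be undertaken to determine the incremental costs and outcomes associated with the intervention relative to controls". It goes on to cost-effectiveness ratios with confidence intervals, acceptability curves and sensitivity analyses. It gives no model and no covariates.

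The general paragraph of Data analysis is more specific. Continuous variables get independent t-tests, other tests may be used where the data call for them, and confounding baseline variables are to be corrected by logistic regression. No other adjustment method appears in the protocol.

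The Trial data collection section lists EQ-5D-5L among the baseline assessments, together with "healthcare utilization (linkage data from Australian Pharmaceutical benefits Scheme and Medicare Benefits Schedule". Outcome measures follow at 3, 6 and 9 months.

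**The concern.** A QALY built from EQ-5D-5L at baseline and three follow-up visits contains the baseline value as one of its terms, and that value also predicts the later ones. If the arms differ at baseline by chance, part of the difference reappears in an unadjusted incremental QALY and then in the denominator of the cost per QALY. The usual remedy is a linear model with baseline utility as a covariate.

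The protocol does foresee correcting for baseline variables, but the tool it names is for binary outcomes. An analyst who follows the text has no usable adjustment for QALYs or costs and falls back on the t-test. A later analysis plan written to match the protocol would inherit the mismatch. At stake are precision and the handling of chance imbalance in the economic result.

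**Working it through.** **Inputs from the protocol.** Allocation: "Participants will be randomly allocated in a 1:1 ratio to either intervention or control group arms". Size: "allowing for a 20 % loss to follow up, a total of 220 participants will be recruited", that is 110 per arm. Visits: baseline, 3, 6 and 9 months.

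**Reproducing the plan's own figure.** The protocol states no figure for QALYs or costs, so only the sample size can be reproduced.
- Means: for "an absolute increase in mean adherence of 15" percentage points, "at two tailed 0.05 significance level with a power of 80 % and standard deviation of 35", n = 2 × (1.96 + 0.84)² × 35² / 15² ≈ 86 per group, as stated.
- Proportions: for "an increase in the proportion of adherent participants from 60 % to 80" per cent, the continuity-corrected formula gives 91 per arm, 182 in total, as stated.
- Loss to follow-up: 91 × 1.2 = 109.2, rounded up to 110 per arm, 220 in total, as stated.

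**Assumptions, because the protocol gives no values.** Trapezoidal QALYs; EQ-5D-5L SD 0.20 (range 0.15 to 0.25), equal at all visits; the same correlation ρ between any two visits, 0.6 (range 0.5 to 0.7); complete data.

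**Step 1, weights.** In years, the visits at 0, 3, 6 and 9 months have weights 0.125, 0.25, 0.25 and 0.125, which sum to 0.75. Baseline has 0.125 / 0.75 = one sixth of the weight.

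**Step 2, size of a chance gap.** The standard error of the baseline difference is SD × √(2/110) = SD × 0.135. This is 0.020, 0.027 and 0.034 at SD 0.15, 0.20 and 0.25.

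**Step 3, how much is carried over.** The slope of QALY on baseline utility is 0.125 + 0.625ρ. A one-standard-error gap therefore shifts the unadjusted increment by:
- SD 0.15, ρ 0.5: 0.0202 × 0.4375 = 0.009 QALY
- SD 0.20, ρ 0.6: 0.0270 × 0.50 = 0.0135 QALY
- SD 0.25, ρ 0.7: 0.0337 × 0.5625 = 0.019 QALY

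In the central case only 0.125 × 0.027 = 0.0034 comes from baseline being a term of the QALY. The remaining 0.0101 comes from the assumed correlation with later visits.

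**Step 4, precision.** The QALY variance is SD² × (0.15625 + 0.40625ρ). The share explained by baseline is slope² divided by the bracket.

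| ρ | slope | variance / SD² | variance removed | variance left |
|---|---|---|---|---|
| 0.5 | 0.4375 | 0.359 | 53% | 0.467 |
| 0.6 | 0.5000 | 0.400 | 62.5% | 0.375 |
| 0.7 | 0.5625 | 0.441 | 72% | 0.282 |

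At SD 0.20 and ρ 0.6 the standard error of the incremental QALY falls from 0.0171 to 0.0104. At ρ 0.5 the gain already equals 1 / 0.467 = 2.1 times the sample for this estimate.

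**Step 5, bias and coverage.** A simulation with normal data, no true difference, SD 0.25, ρ 0.6 and 110 per arm (8,000 runs) gave this coverage for the 95% interval:

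| trials counted | unadjusted | adjusted |
|---|---|---|
| all | 95.3% | 94.9% |
| baseline gap above 1 SE | 86.6% | 94.9% |
| baseline gap above 1.96 SE | 56.2% | 95.4% |

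The mean unadjusted estimate over all runs was 0.000.

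**The case against.** The strongest reply is that the economic text is silent on its estimator. A participant-level analysis is compatible with regression on baseline utility, and covariates for such a model are commonly left to a statistical or health-economics plan, which is not at hand. The t-test rule sits in a general paragraph about the primary analyses at each time point, whereas the economic outcomes have their own text and a commitment to best practice.

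Much of this stands. A reader might infer that the protocol plans plain differences between arms for QALYs and costs; no sentence says so, and silence alone would be no finding. What remains is that the protocol does commit itself on baseline correction, and the one method it names does not fit these outcomes. The allowance for other tests offers tests, not a covariate model.

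Three other stronger readings also fail:
- **That the unadjusted result is biased.** Over all randomisations it is not, and its interval has nominal coverage. The loss is in precision and in accuracy given an observed gap.
- **That imbalance could match the expected QALY gain or reverse its sign.** The protocol states no expected gain, so there is no benchmark for this.
- **That cost should equally be adjusted for pre-trial linked use.** No look-back window is stated, so pre-trial use is itself an inference. Linkage needs separate consent (Ethics and dissemination). Admissions come from medical records, while the Introduction names repeated admissions as a main driver of heart failure spending. With assumed correlations of 0.3 to 0.7, the gain would be 0.3² to 0.7², a 9 to 49% cut in cost variance.

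**Conclusion.** The point holds as a mismatch of method. The protocol's only stated baseline correction cannot be applied to QALYs or costs, and the economic text supplies no alternative, although the covariate that matters most for QALYs is collected. Under SD 0.15 to 0.25, ρ 0.5 to 0.7, trapezoidal QALYs and 110 analysed per arm, a one-standard-error baseline gap carries about 0.009 to 0.019 QALY, and adjustment removes about 53 to 72% of the variance. These sizes rest on assumed variability and correlation. Fewer analysed participants would enlarge the chance gap: with 20% lost, 88 per arm and SD 0.20, its standard error is 0.20 × √(2/88) = 0.030 instead of 0.027. The primary adherence comparison is outside this point. The change is worth making because it costs almost nothing.

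**What to change.** In Data analysis, Economic outcomes:
- State that the incremental QALY is estimated by linear regression of QALY on arm and baseline EQ-5D-5L, with the covariate fixed in advance and not chosen after inspecting imbalance.
- Bootstrap the adjusted incremental QALY jointly with incremental cost, resampling participants, for the interval of the cost-effectiveness ratio and the acceptability curve.
- Report the unadjusted difference alongside.
- In the general paragraph, confine logistic regression to binary outcomes.

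Adjusting cost for prior linked PBS/MBS cost is optional. If it is wanted, define the look-back window, say how participants who decline linkage are handled, and acknowledge that the covariate does not capture hospital admissions.

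The QALY change needs analysis wording only. Baseline EQ-5D-5L is already collected, so no visit or questionnaire is added. The optional cost covariate also needs a defined linkage period.

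### The economic analysis plans confidence intervals for the ICER itself; these become unbounded or unreadable if the 9-month QALY difference is not clear of zero, so net monetary benefit should carry the uncertainty

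*Protocol*

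**What the plan says.** The Economic evaluation section sets up a cost-utility analysis with "quality adjusted life years gained (QALYs) as measured by the EQ-5D-5L as the main measure of outcome", run alongside "the clinical trial with a 9 month follow up period". Of the comparison between arms it says: "This will be expressed in terms of the incremental cost per QALY gained in the Australian setting".

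The Economic outcomes part of Data analysis then fixes how uncertainty is shown: "Incremental cost effectiveness ratios and their associated confidence intervals will be estimated". The same sentence adds that "cost effectiveness acceptability curves for varying threshold values of cost effectiveness will also be presented", and the next promises an assessment of sensitivity "using appropriate one-way, multi-way and probabilistic sensitivity analysis". The sentence before these plans a participant-level analysis of incremental costs and outcomes.

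The protocol does not name net monetary benefit or a method for the ICER interval. It gives no expected QALY difference, utility SD, cost SD or willingness-to-pay value. Cost-effectiveness is the first of the secondary aims in the Hypothesis section. The Sample size section deals only with adherence: "a total sample size of 182 participants is needed to provide 80 % power to detect an increase in the proportion of adherent participants".

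**The concern.** An interval for a ratio behaves well only when the denominator is clearly different from zero. Here the denominator is a difference in QALYs accrued over nine months, in a trial whose size was chosen for a different outcome.

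Two things go wrong when that difference is uncertain. First, Fieller's method gives no finite pair of limits: the 95% set is either the whole line or everything outside a gap. Second, a method that always returns finite limits, such as a bootstrap percentile interval, gets them by ranking ratios from all four quadrants of the cost-effectiveness plane on one scale. A negative ratio can mean that the intervention saves money and improves health, or that it costs more and harms health. A positive ratio can likewise come from opposite corners. Limits taken from such a ranking have no decision meaning.

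The protocol commits to the interval on the ratio and has no rule for an uncertain QALY difference. The main economic result could then carry error bars that cannot be read, with no interval on a scale where one always exists.

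**Working it through.** **The plan's own figures.** There is no planned figure for the ICER or the QALY difference, so only the sample size can be reproduced. For a 15-point difference with SD 35, n = 2(1.96 + 0.84)² × 35²/15² ≈ 86 per group, as stated. For 60% against 80% adherent, the continuity-corrected formula gives 91 per arm, 182 in total, as stated. Both concern adherence. The recruited 110 per arm less the stated 20% loss leaves 110 × 0.8 = 88 per arm.

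**When the Fieller interval is bounded.** Write Δq and Δc for the QALY and cost differences, with standard errors s_q and s_c. The 95% limits solve a quadratic whose leading coefficient is a = Δq² − 1.96² s_q². The limits enclose a bounded interval only if a > 0, that is, only if the 95% interval for Δq excludes zero.

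**How often a > 0 fails.** Assumptions, none from the protocol: QALY SD 0.10, 0.15 or 0.20; true gain 0.02 or 0.04 QALY; normal sampling. Then s_q = SD × √(2/88), and the chance that the QALY interval includes zero is Φ(1.96 − gain/s_q) − Φ(−1.96 − gain/s_q).

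| QALY SD | s_q | Gain 0.02 | Gain 0.04 |
|---|---|---|---|
| 0.10 | 0.0151 | 74% | 24% |
| 0.15 | 0.0226 | 86% | 58% |
| 0.20 | 0.0302 | 90% | 74% |

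At a true gain of 0.02, the estimated QALY difference is zero or negative with probability Φ(−0.02/s_q): 9%, 19% and 25% for the three SDs.

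The same check on the utility scale, with 91 per arm, utility SD 0.10 to 0.25 and s_q = 0.75 × SD × √(2/91), shows how strongly the result depends on the effect. The chance that the interval includes zero is 73–92% for a true utility difference of 0.02, 8–73% for 0.05, and 0–42% for 0.08.

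**One worked example.** All inputs are assumed: 91 per arm, utility SD 0.20, utility difference 0.02, cost difference AUD 500, cost SD AUD 10,000, correlation 0.

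- Δq = 0.75 × 0.02 = 0.015; s_q = 0.75 × 0.20 × √(2/91) = 0.0222; s_c = 10,000 × √(2/91) = 1,482.
- Fieller: a = −0.00167 and the discriminant is −13,665. Both are negative, so the 95% set is the whole real line.
- Percentile limits of the ratio from 100,000 simulated cost and QALY pairs: about −691,000 to +746,000 per QALY. In 25% of pairs the QALY difference is negative. Negative ratios mix 27% of pairs that save money and gain QALYs with 16% that cost more and lose QALYs.
- Incremental net monetary benefit is λΔq − Δc, with standard error √(λ²s_q² + s_c²) at zero correlation. At an assumed λ of AUD 28,000 it is 420 − 500 = −80 (95% CI −3,232 to 3,072). At an assumed λ of AUD 50,000 it is 750 − 500 = 250 (−3,382 to 3,882). Both intervals are finite and can be read directly.

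**Where the ratio interval does work.** With the utility difference raised to 0.08 (Δq = 0.06) and the rest unchanged, Δq/s_q = 2.70, a is positive, and Fieller gives −53,979 to 89,267 per QALY. That interval is valid. It includes negative ratios, which here mean cost saving, so the quadrant still has to be stated.

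**The case against.** The strongest reply has four parts.

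- **Other outputs are planned.** Incremental costs and outcomes will be determined, and their signs identify the quadrant. An acceptability curve is, at each threshold, the probability that net monetary benefit is positive. This stands. A reader might infer that users of the results could not tell a dominant intervention from a dominated one; the documents do not support that. What the curve lacks is an estimate of the size of net benefit and an interval for it.
- **No interval method is named.** An unbounded Fieller set is not an error: it keeps its coverage and says honestly that the data do not bound the ratio. The mixing of quadrants belongs to percentile limits, which the protocol does not specify, and the method may properly be left to a later plan. This stands as to method. But the choice to put the interval on the ratio is made in the protocol, and no method yields a bounded and interpretable interval when the QALY difference is not clear of zero.
- **The frequency rests on assumed inputs.** This stands fully. A reader might infer that the interval fails in most plausible scenarios. The protocol gives no QALY effect or SD to support that, and moving the assumed gain from 0.02 to 0.04 takes the range from 74–90% to 24–74%.
- **An ICER interval is sometimes valid.** This also stands: when the QALY difference is clear of zero, a Fieller interval is bounded and sound. A rule that no ICER interval may ever be reported would go too far.

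**Conclusion.** The concern holds in a limited form. The protocol places confidence intervals on a ratio whose denominator the trial was not sized to estimate, and has no provision for the case where that denominator is not separated from zero. In that case the interval is unbounded (Fieller) or not interpretable (percentile limits). The algebra does not depend on assumed inputs; the frequency does. With 88 per arm and a QALY SD of 0.10 to 0.20 it is about 74–90% at a true gain of 0.02 QALY and about 24–74% at 0.04, and it falls further for larger effects. It should not be read as a prediction that the interval will fail.

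The planned acceptability curves and incremental results already convey part of the uncertainty. Cost-effectiveness is a secondary aim, and neither the adherence comparison nor the data collection is affected. This is a minor point, worth making because the better method needs no new data.

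**What to change.** Amend the sentence in Data analysis, Economic outcomes, along these lines:

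> Incremental cost and incremental QALYs will each be reported with a 95% confidence interval. Incremental net monetary benefit with a 95% confidence interval, at stated willingness-to-pay values, will be the main measure of uncertainty, shown with the acceptability curve. The ICER will be given as a point estimate with its quadrant. An interval for the ICER will be given only if the 95% interval for incremental QALYs excludes zero.

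The willingness-to-pay values should be written down before the data are analysed; the two used in the working are illustrations, not proposals. The cost is a short change of text. The net-benefit intervals come from the same draws of cost and QALY differences that the acceptability curve needs, so no further data and almost no further analysis are required.
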